## Abstract

**Background:**

Sexual and gender minority (SGM) adolescents who can benefit from HIV testing due to their sexual behavior (eg, condomless anal or vaginal sex) report suboptimal HIV testing rates. However, interventions designed to increase HIV testing rates among SGM adolescents are lacking, and even when effective interventions exist, reaching SGM adolescents outside research settings can be a challenge. This hybrid type 1 study aims to evaluate the effectiveness of Sharing Health Education Resources (SHER), a multimedia messaging service (MMS) intervention in increasing adolescent HIV testing rates and to address implementation challenges of reaching and engaging SGM adolescents in digital interventions in real-world settings.

**Objective:**

This study first aims to adapt a digital sexual health intervention previously designed for adolescent sexual minority males to be inclusive of all SGM adolescents and reflect new advancements in HIV prevention science. The second aim is to test the adapted intervention through a hybrid type-1 effectiveness-implementation randomized controlled trial (RCT) with the primary outcome of HIV testing. The third aim is to gather expert recommendations on how to best reach and engage SGM adolescents outside of research settings.

**Methods:**

SHER is guided by the information-motivation-behavioral skills theory and expands upon a previous intervention tested in a 2014 pilot trial. The previous version of the intervention significantly increased self-reported HIV testing among adolescent sexual minority males compared to an information-only control. Updates to this intervention in this study were driven by stakeholder and adolescent feedback and included modernizing technology, content, and gender inclusivity. An RCT will compare the impact of SHER versus an information-only control condition on HIV testing rates among 360 US SGM adolescents aged 13‐19 years. The implementation aim is focused on understanding expert and adolescent perspectives on best practices for reaching and engaging SGM adolescents outside of research settings.

**Results:**

Data collection regarding intervention updates was concluded in January 2025 with publication of results planned in fall 2026. As of April 2026, 295 participants have been enrolled into the RCT, with the conclusion of data collection, analysis, and publication of results planned for Winter 2027. All data collection regarding best practices for reaching and engaging SGM adolescents outside of research settings was completed in September 2025, with publication of results planned for Summer 2026.

**Conclusions:**

This study will evaluate whether an MMS messaging intervention based on health behavior change theory will increase SGM adolescent HIV testing relative to an information-only version of this intervention. This study will also produce expert- and adolescent-informed best practices for reaching SGM adolescents for sexual health interventions in real-world settings. Overall, this study aims to contribute to increased engagement in sexual health care and HIV testing in SGM adolescents engaging in HIV transmission risk behaviors.

## Introduction

In the United States, an estimated 44% of youth aged 13‐24 years who are HIV-positive are unaware of their status, making this the group with the highest proportion of undetected HIV infections across all age brackets [1-3]. Even though clinical and public health recommendations suggest screening for HIV at least once between the ages of 15 years and 21 years [4], yearly for those engaging in HIV transmission risk behavior (eg, condomless penetrative sex without HIV pre-exposure prophylaxis [PrEP]) [5], and every 3-6 months for sexually active men who have sex with men [5], testing rates do not reflect these guidelines [6]. This issue is particularly pronounced among sexual and gender minority (SGM) adolescents, with only 1 in 4 gay and bisexual teenage boys [7], approximately 1 in 7 transgender adolescents [8], and variable rates among sexual minority girls, ranging from just 1 in 40 girls who have sex with girls only to 1 in 4 girls who have sex with both boys and girls [9] reporting HIV testing. However, programs aimed at increasing HIV testing predominantly focus on adults and heterosexual, cisgender youth [10-13], which may not address the unique barriers faced by SGM adolescents, such as fear of being outed, anticipated stigma and discrimination in health care settings, and developmental concerns about navigating sexual identity while accessing sexual health services.

Digital interventions delivered via smartphones offer a promising strategy for reaching SGM adolescents, as 95% of adolescents report using smartphones and rely on texting to communicate [14]. Compared to app-based interventions, those delivered via multimedia messaging service (MMS) are more accessible, scalable, and easy to use [15-19]. Further, they can be more cost-efficient, require minimal data, and perform reliably across operating systems. These features make MMS-based interventions well-suited to addressing structural barriers, including transportation limitations, restrictive clinic hours, geographic isolation, financial constraints, or confidentiality concerns, that often limit access to in-person and web-based services, which disproportionately affect Black and Latino youth and those in lower-resourced communities [20-22].

Despite these advantages, few studies have explored considerations for implementing MMS-based HIV prevention programs in real-world settings [23,24]. In an ever-changing sociotechnical environment, digital interventions designed to be tested in research studies (and not necessarily with real-world implementation in mind) may change little over the course of several years. These interventions often fail to keep up with real-world user expectations of technology and design and thus seem quickly dated. In addition, in fields like sexual health and HIV, new innovations occur often and necessitate changes to intervention content to remain medically accurate. Moreover, it is not enough to build an effective digital intervention and leave it on the shelf. Implementers must be able to successfully reach and engage desired users once the intervention is deployed in the real world. For digital interventions on sensitive topics like adolescent sexual health to succeed, it is critical to reach and build trust with youth where they already are (ie, online). However, this task can be daunting for organizations who seek to engage SGM adolescents, as the online spaces where SGM adolescents spend their time change quickly, and advertising to or reaching minors can be expensive, and platforms’ policies regarding advertising can be opaque or change often, which can constrain organizations’ ability to reach this group.

Studies that examine both how well digital HIV prevention and testing interventions for adolescent populations work and how to overcome real-world implementation challenges like reaching SGM adolescents are needed to address the domestic HIV epidemic. In response, this paper describes the protocol for a type 1 hybrid study to evaluate the effectiveness and implementation of an adapted version of Guy2Guy (G2G), an SMS text messaging–based HIV prevention program originally developed in 2013‐2014 for cisgender gay, bisexual, and queer adolescent boys [25-27].

G2G was grounded in the information-motivation-behavioral skills model, which proposes that health behavior change requires not only information about the target behavior but also motivation and skills to engage in the behavior [28-31]. G2G’s active condition was comprised of 5 weeks of 8‐10 daily automated SMS text messaging pushed to adolescents’ phones. Six weeks later, participants were given a week of booster content to reinforce what they had learned. These messages aimed to decrease condomless sex (the primary outcome) and increase HIV prevention knowledge, motivation, self-efficacy, and HIV and sexually transmitted infection (STI) testing behavior (secondary outcomes). The intervention condition also included several interactive elements to promote engagement, including quizzes to test information retention, a question-and-answer feature called G2Genie that enabled participants to request additional texts on a circumscribed number of topics that were ancillary to the primary intervention content (eg, relationships), and badges. Finally, participants were matched with an anonymous “Text Buddy” (another participant in the program) to encourage social support and engagement. G2G’s control condition was an information-only, healthy lifestyle control that did not include interactive components. A pilot randomized controlled trial (RCT) demonstrated G2G’s feasibility, acceptability, and preliminary efficacy, whereby the intervention condition was associated with a 3-fold increase in HIV testing, but no significant difference in condomless sex behaviors compared to the control condition [25-27].

This study was motivated by the question of whether the G2G intervention, if updated and repackaged to focus more on HIV testing, could be effective among a broader group of SGM adolescents who may benefit from HIV testing based on their sexual history. First, we aimed to systematically adapt G2G’s content and delivery to refocus the content on HIV testing as a primary outcome [25-27]. We also sought to reflect significant advancements since the pilot RCT in digital technologies, HIV prevention science, and changes in youth and SGM culture, and to make the intervention content more inclusive of SGM adolescent populations underrepresented in HIV prevention and testing research [32]. Our second aim was to evaluate the intervention’s effectiveness on the new primary outcome of HIV testing and secondary outcomes related to sexual health care engagement, such as PrEP uptake and STI testing, via a nationwide RCT among SGM adolescents. We hypothesized that participants in the intervention condition would be more likely to report HIV testing at least once during the 9-month study period than participants in the control condition. Finally, our third aim engaged experts and adolescents to identify key strategies for reaching and engaging SGM adolescents for digital sexual health interventions in real-world settings. This study is in progress, and of note, after the study launched, various challenges led to modifications of study activities originally proposed in the grant, which will be described in this protocol paper.

## Methods

### Study Overview

This study uses a type 1 hybrid effectiveness-implementation design [33], which primarily tests the intervention’s effectiveness and secondarily explores barriers and facilitators to future implementation. As the study is ongoing, verb tenses in the methods section may be in past or present tense depending on activity completion status. Here we provide an overview of the study aims, and the methods in each aim are described in more detail in the sections below (see Figure 1).

**Figure 1. F1:**
[figure not shown]
An overview of the study aims with their respective activities and main outcomes. PrEP: pre-exposure prophylaxis; STI: sexually transmitted infection.

#### Aim 1

From 2022 to 2024 we adapted and modernized G2G content and rebranded the intervention as Sharing Health Education Resources (SHER), which is inclusive of diverse gender identities and reflects HIV testing and prevention innovations since the original G2G RCT. This process was guided by an adolescent advisory council and by pre-implementation interviews with adults who had experience working with SGM adolescents in clinical, educational, and community settings. End user and implementer input was sought to ensure that the intervention content was relevant to adolescents and to increase the likelihood of uptake in real-world settings.

#### Aim 2

From 2024 to 2026 we are conducting a nationwide RCT with SGM adolescents aged 13‐19 years (proposed n=360) to test the effectiveness of SHER compared to an information-only control arm. The primary effectiveness outcomes include objective and self-reported HIV testing, and secondary effectiveness outcomes include sexual health care engagement behaviors, such as PrEP uptake and STI testing. We are enrolling a diverse sample to reflect demographic groups who could benefit from HIV testing yet are underrepresented in adolescent HIV research (eg, Black and Latino youth; transgender and gender-diverse youth; and cisgender girls).

#### Aim 3

In 2025, we gathered feedback from individuals with expertise in reaching and engaging SGM youth in clinical, educational, or community settings; implementing SGM-inclusive sexual health education initiatives; or implementing digital interventions in real-world settings. Through engagement with these experts and SGM adolescents, we identified implementation strategies that effectively address barriers and facilitators to reaching and engaging SGM adolescents for real-world digital interventions and will develop consensus recommendations for dissemination.

### Approach for Aim 1

#### Initial Content and Software Adaptation Phase

##### Content Adaptation

Content revisions followed a modified ADAPT-ITT (assessment, decision, adaptation, production, topical experts, integration, training, and testing) framework [34], a stepwise model for adapting evidence-based HIV interventions. As the first 3 steps of ADAPT-ITT were complete (assess the needs of the target population, decide whether to adopt or adapt interventions, and, if adapting, use a methodology to guide adaptation), we began with the production phase, whereby we created an adaptation plan and determined our adaptation goals. In the following sections of Aim 1 and 2, we allude to other steps of ADAPT-ITT (topical experts to provide content and technical assistance, integrate all forms of information, train personnel, and test for adaptation effectiveness).

First, content from the original G2G program was reviewed by the study team, who consisted of investigators and staff with expertise in SGM adolescent health, HIV prevention, and mental health. The goals were to identify texts that were scientifically outdated, did not reflect contemporary language used by SGM adolescents, or were specific to cisgender boys (eg, references to “guys” and anatomy). Further, reviewers identified possible areas where content focused on HIV testing and other topics desired by youth who completed the G2G pilot trial (eg, relationships and consent) could be expanded. SMS text messages were drafted to address these content areas based on up-to-date scientific knowledge, focusing more on sexual health care engagement outcomes (eg, HIV testing and PrEP) and less on condoms, and were more gender inclusive. To accommodate expanded content and topics such as mental health, communication, and relationships requested by participants from the G2G pilot RCT, we extended the intervention and control arms by 1 additional week. The adapted intervention resulted in roughly 6 weeks of daily SMS text messaging and MMS messages, plus a weeklong booster 6 weeks after this content concluded.

##### Technological Components

The ADAPT-ITT framework was complemented by the Trials of Intervention Principles model [35]. This framework allows intervention developers to assess whether technological or interactive features of a digital intervention can be changed or updated to meet user expectations and preferences without sacrificing the mechanism of behavior change, and enables interventionists to specify how, when, and why technological components are delivered. The study team identified the technical instantiations of the original G2G—SMS text messaging, quizzes, polls, badges, G2Genie, and Text Buddy—and explored which elements were critical to intervention delivery (SMS text messaging) and which elements could be modified to meet modern expectations of technology and youth culture to increase engagement (quizzes, polls, badges, G2Genie, and Text Buddy).

To make quizzes and polls more engaging and meaningful, we developed prototypes whereby participants could earn points that can be exchanged for prizes at the end of the 6-week intervention period; these points replaced the badges in the original G2G. G2Genie enabled participants to text one of several keywords (eg, “relationships”), after which the program would send several SMS text messages about this topic; these texts were static and not updated. To reflect more contemporary online health information-seeking behaviors and technology, we chose to embed links to Planned Parenthood of America’s “Roo,” an artificial intelligence (AI)–powered, evidence-based sexual health chatbot designed for youth that offers dynamic responses to sexual and relationship health questions in real time [36]. Finally, youth in G2G were inconsistently engaged with their Text Buddies [25]; in response, this feature was changed to a group chat where participants are assigned a group of 3‐5 individuals rather than one person to reduce social pressure.

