##### Control Condition

The information-only control group receives the same number of MMS messages and interactive features as the intervention group, over the same amount of time, but does not receive motivational or behavioral skills content. The content, outlined in Figure 2, covers information on physical, social, mental, and sexual health.

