#### Changes to Sample Size (August 2025-March 2026)

In summer 2025, although the enrollment rate increased, it was not enough to compensate for the time lost in the earlier months of the RCT, and the team was experiencing several additional challenges. First, there was uncertainty about whether the project would continue to be funded by NIH due to changes in federal funding priorities, and the grant budget had been reduced substantially. Furthermore, RCT and Aim 3 activities were occurring simultaneously due to the recruitment delays, requiring study staff to manage competing priorities. In addition, the longer recruitment lasted, the more costs would be incurred for advertising and retention. These factors led the investigative team to explore the feasibility of reducing the sample size to conserve resources and ensure completion of the trial before the end of the grant period.

Power calculations were performed using nominal type I error rates (α=.05) and assumed a 1:1 allocation to each study arm and identical arm-specific retention rates. The assumed HIV testing rate for control participants at the final time point was 28% based on previous findings from the G2G pilot study [26]. The original sample size proposed in the grant (n=360) was chosen to power comparisons at the end of the trial. Assuming 80% retention, the study would be 81% powered to detect a small to medium intervention effect for self-reported or objective HIV testing. Revised power calculations were conducted in August 2025 by a biostatistician. It was concluded that, assuming study endpoint retention rates of 90% or higher, the study’s target sample size could be reduced from 360 to 310 and maintain the 80% power to detect differences between the intervention and control groups at the same magnitude that was targeted in the original power analysis. At the time of these analyses, study retention was at or near 90% and, in March 2026, exceeded 90%. The sample size reduction and expanded inclusion criteria will likely limit the ability to conduct adequately powered subgroup analyses, so those analyses will be treated as exploratory. However, maintaining the higher targeted retention rate should allow for mediation analysis at similar power levels as the originally targeted sample size. Assuming these recruitment rates hold, we anticipate completing recruitment by June 2026 and retention efforts by January 2027.

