#### Quantitative Analysis

We hypothesize that participants in the SHER intervention and control groups will differ in whether they are tested for HIV during the study and that HIV prevention, testing, and treatment information, motivation, and behavioral skills will mediate these effects (Table 1). Our secondary outcomes will include PrEP initiation; discussion with providers about HIV, STI testing, and PrEP; and frequency of receptive or insertive condomless sex and STI testing.

We will assess the experimental and control groups’ similarities at baseline. Variables that differ significantly will be covariates in adjusted outcome analyses, along with variables correlated with the outcome (eg, age), as well as covariates associated with missingness in order to address differences in attrition [70-74]. The primary outcome will be analyzed using a generalized linear mixed effects model that assumes a binomial distribution and logit link. The generalized linear mixed effects model will incorporate data from baseline, 3-month, and 6-month follow-ups and account for both fixed and random effects over time. Residual diagnostics will be used to evaluate model fit, including the possibility of overdispersion. We will report study arm coefficients as log odds ratios and report odds ratio point estimates, SEs, and 95% CIs. The test of the treatment effect will be 2-sided Wald tests that control the type I error rate at α=.05. Missingness will be addressed using either full information maximum likelihood (if missingness is less than 25% as anticipated) or multiple imputation (if missingness is greater than 25%) [75].

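### Participants share group chats of 3-5, but neither the stated primary model nor the stated power inputs allow for correlation within a chat

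*Protocol article*

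**What the plan says.** **Grouping.** Technological Components describes the change from a single Text Buddy: "this feature was changed to a group chat where participants are assigned a group of" 3-5 people. Recruitment Challenges confirms that chat members are other trial participants who interact with each other. Under Control Condition, the control group "receives the same number of MMS messages and interactive features as the intervention group", so chats apparently exist in both arms. Randomization describes individual 1:1 allocation by minimisation and does not mention chats.

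**Analysis.** Quantitative Analysis specifies a binomial-logit mixed model that will "account for both fixed and random effects over time". It adds: "The test of the treatment effect will be 2-sided Wald tests that control the type I error rate at α=.05". It names no chat-group effect or clustered variance.

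**Power.** Changes to Sample Size gives a nominal alpha of .05 and a control testing rate of 28%, and says the calculations "assumed a 1:1 allocation to each study arm and identical arm-specific retention rates". The original design was 360 participants with 80% retention and 81% power. The revised design is 310 with at least 90% retention, said to "maintain the 80% power to detect differences between the intervention and control groups" of the same size as originally targeted. That size is described in words only. No chat size, ICC or design effect is listed.

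**The concern.** This is an individually randomised trial in which part of the intervention is delivered in small groups. Members of a chat share conversations after randomisation, so one member's decision to test may influence another's. Random effects over time deal with repeated measurements on the same person. They do not deal with similarity between different people in one chat.

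If that similarity is positive and each chat lies wholly within one arm, the variance of the arm contrast is larger than the stated model recognises. The Wald test would then reject too often under the null, and the type I error control claimed in Quantitative Analysis would not be met exactly. The power argument for cutting the sample to 310 would also be optimistic, and at 90% retention that argument has no slack.

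**Working it through.** **Inputs from the article:** control rate 28%; alpha .05, two-sided; 1:1 allocation; 360 at 80% retention with 81% power; 310 at 90% retention with 80% power; chats of 3-5.

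**Inputs assumed:** ICC from 0 to 0.10; mean chat size m = 4; chats formed within arm; the comparison simplified to two proportions at the endpoint.

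**Step 1: recover the effect.** The original design gives 360 × 0.80 / 2 = 144 per arm. The two-proportion normal approximation is

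power = Φ{ [d√n − 1.96√(2·p̄·(1−p̄))] / √(p₁(1−p₁) + p₂(1−p₂)) }, where d = p₂ − p₁.

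Setting p₁ = 0.28, n = 144 and power = 0.81 gives p₂ = 0.440, an odds ratio of about 2.02.

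**Step 2: reproduce the stated power.** The revised design gives 310 × 0.90 / 2 = 139.5 per arm. With p₂ = 0.440, power is 79.8%, which agrees with the stated 80%. The arcsine and logit-Wald versions, each back-solved in the same way, also give 79.8%.

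**Step 3: apply a design effect.** DE = 1 + (m − 1) × ICC. Power uses 139.5/DE per arm. Type I error with clustering ignored is 2{1 − Φ(1.96/√DE)}. The correct interval is wider than the naive one by a factor √DE. The total needed to restore planned power is 310 × DE.

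| ICC (assumed) | DE, m=4 | Power at n=310 | Naive type I error | Interval should be wider by | Total n needed |
|---|---|---|---|---|---|
| 0 | 1.00 | 79.8% | 5.0% | 0% | 310 |
| 0.01 | 1.03 | 78.6% | 5.3% | 1.5% | 320 |
| 0.02 | 1.06 | 77.4% | 5.7% | 3.0% | 329 |
| 0.05 | 1.15 | 74.0% | 6.8% | 7.2% | 357 |
| 0.10 | 1.30 | 68.7% | 8.6% | 14.0% | 403 |

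Across chat sizes of 3 to 5, power is 76.6-78.2% at ICC 0.02, 72.1-75.9% at 0.05 and 65.4-72.1% at 0.10.

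**Step 4: check by simulation.** With 35 chats of four per arm, an endpoint comparison and a Wald test that ignores chats, type I error was 4.6%, 5.7%, 6.3% and 8.3% at ICC 0, 0.02, 0.05 and 0.10. Coverage of the nominal 95% interval at the back-solved effect was 95.0%, 94.1%, 93.5% and 91.5%.

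**Step 5: allow for attrition and better retention.** With 10% attrition, a chat of four leaves 4 × 0.9 = 3.6 analysed members, so at ICC 0.05 the design effect is 1 + 2.6 × 0.05 = 1.13, not 1.15. At 95% retention there are 310 × 0.95 / 2 = 147.25 per arm, and power without clustering is 81.9%. Since 147.25 / 139.5 = 1.056, that would absorb a design effect of about 1.05.

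**The case against.** The strongest reply is that independence is inferred from silence. The article gives one sentence on random effects and does not exclude a chat-group term, and a full specification may sit in a document that is not shown. Reproducing the 80% does not prove that clustering was ignored either: with the effect unstated, a constant design effect would cancel in Step 2. Both points stand as limits on certainty. They do not remove the concern, because the model as stated would be wrong under the conditions named, while the article claims error control for it and lists the inputs behind the cut to 310.

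A reader might go further and infer that outcomes are correlated by design, so that intervals are too narrow and power is overstated as a matter of fact. The article does not support this:

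- It gives no ICC, and at ICC 0 nothing changes.
- It does not say that chat members discuss sexual health. The social-support purpose is stated in the Introduction for the pilot's Text Buddy. The reason given for the group format is to lessen social pressure, after youth engaged inconsistently with their buddies. Low chat use and an ICC near zero are compatible with that.
- It does not say that chats are arm-specific. Withholding motivational and skills content from controls and blinding participants to version both make this the likelier reading. If chats mix arms, the main problem is contamination, and the interval for the arm contrast would not be too narrow.

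Retention above 90%, reported for March 2026, also offsets a small part of any loss.

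**Conclusion.** The point holds in conditional form. The article describes grouped, interacting participants and names nothing in its primary model or power inputs to allow for correlation within a chat. If chats are arm-specific and the ICC is positive, the stated analysis is somewhat anti-conservative and the stated power somewhat high.

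The size depends on an ICC that nobody has stated. At 0.01-0.02 the loss is about 1 to 3 points of power and type I error stays below 6%. At 0.05-0.10 the loss is about 4 to 14 points across chat sizes of 3 to 5. These figures also rest on the back-solved 44% and on 90% retention. Confidence is high that the stated text has no provision for chats, and only moderate about how much it matters.

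**What to change.** 1. State whether chats are formed within arm.
2. If they are, specify before analysis that the primary treatment test uses standard errors clustered on chat group, with ungrouped participants as singletons. A chat-group random intercept is an alternative if it converges.
3. Report the estimated ICC, and restate the power for n=310 over an assumed range such as 0-0.05, giving the target effect as a number.
4. If chats mix arms, say how contamination between arms will be addressed instead.

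No new data should be needed. Data Security and Participant Safety says that group texts pass through the study server and are recorded, so membership should be recoverable. The analysis is still to come, so the change can be prespecified.

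The cost is slightly wider intervals and a slightly lower stated power. The random-intercept version may have convergence trouble, because it adds a third level to a binary model with clusters of about four, and its odds ratio would be conditional on chat as well as on person. Clustered standard errors are the simpler choice.
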